## 5.2.1 Outline of Study Procedures

### Procedure 1: Screening

- SPT, TNSS, PnIF
- Intranasal Challenge.
- Spirometry, ASS (in asthmatics)

↓ > 2 weeks

### Procedure 2: Baseline Tests

- Clinical examination, TNSS, PnIF
- Modified Intranasal Challenge, TNSS, PnIF
- Spirometry, ASS (in asthmatics)

Nasal lavage (0, 0.5, \*[6-8], 24hr)

- Measure IL-1 $\alpha$ , IL-4, IL-5, IL-13, tryptase, ECP, TSLP, SCF

\*[6-8]=subgroup able to attend

Nasal Scrapings (0, 24hr)

*Cytospins*

- Differential count

*Epithelial cell cultures*

- Analysis CD80, CD86, OX40L, CD117
- CD117, IgE, tryptase, chymase
- Soluble cytokine receptors

Peripheral Blood (0, 24hr)

- Serum pollen-specific IgE, sCD23
- Stimulated cultures FceR1 on DC
- Unstimulated cultures FceR1 on Dc

↓ 16 weeks from Base-line tests

### Procedure 3: Post-Intervention

- Clinical examination, TNSS, PnIF
- Modified Intranasal Challenge, TNSS, PnIF
- Spirometry, ASS (in asthmatics)

Nasal lavage (0, 0.5, \*[6-8], 24hr)

- Measure IL-1 $\alpha$ , IL-4, IL-5, IL-13, tryptase, ECP, TSLP, SCF

\*[6-8]=subgroup able to attend

Nasal Scrapings (0, 24hr)

*Cytospins*

- Differential count

*Epithelial cell cultures*

- Analysis CD80, CD86, OX40L, CD117
- CD117, IgE, tryptase, chymase
- Soluble cytokine receptors

Peripheral Blood (0, 24hr)

- Serum pollen-specific IgE, sCD23
- Stimulated cultures FceR1 on DC
- Unstimulated cultures FceR1 on Dc

### 5.3. Study subjects

#### 5.3.1. Number of Subjects/Controls

In this study, 30 participants will receive the active drink and 30 the control placebo preparation, (a similar milk drink without any probiotic bacteria).

#### 5.3.2. Setting

All participants will attend Clinical Research Trials Unit (CRTU) at the Norfolk and Norwich University Hospital for their study procedures.

#### 5.3.3. Inclusion Criteria

Participants to be included will meet the following criteria:

- Men or women >16 years of age.
- A history of SAR for a minimum of 2 years before study entry.
- Documentation of sensitivity by positive skin testing (by prick or intradermal methods) or by adequately validated in vitro tests for specific IgE (e.g., RAST, PRIST) to grass pollen within 12 months prior to enrolment. If this is not available, appropriate tests will be performed at screening.
- Able to provide written informed consent

#### 5.3.4. Exclusion Criteria

The following conditions should exclude possible study participants:

- Ingestion of probiotics as part of normal diet
- Significant medical, surgical or psychiatric disease that in the opinion of the participants' attending physician would affect subject safety or influence the study outcome.
- Symptoms of rhinitis at screening indicated by total symptom scores of more than 2 out of 12 (based on a combination of nasal symptoms of blockage, sneezing, rhinorrhoea and itching).
- Current smokers or ex-smokers of <1 year or those who have smoked the equivalent of 20 cigarettes/day for 20 years or more.
- Participants receiving any form of corticosteroid from 1 month prior to the study
- Inadequate washout periods for the following:
  - Intranasal cromolyn (2 weeks)
  - Intranasal or systemic decongestants (3 days)
  - Intranasal or systemic antihistamines (3 days), except astemizole (6 weeks) or loratadine (10 days).
- Documented evidence of acute or significant chronic sinusitis
- A history of hypersensitivity to the milk or its products
- Pregnant women or those planning a pregnancy. It is important not to include pregnant women in the study due to the possibility of miscarriage following anaphylaxis.
- Lactating women are excluded as those infants breast fed by mothers responding to allergenic challenges can transmit the manifestations of allergic responses to the feeding infant via breast milk

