#### 5. **Study Design**

##### 5.1. **Overview**

This is a, double-blind, placebo-controlled randomised trial to compare Yakult (containing the probiotic strain *Lactobacillus casei* Shirota) with placebo. Participants will attend on 5 to 7 occasions over a 4 to 6 month period for three procedures, all of which will be conducted at a laboratory within the Clinical Trials Research Unit (CRTU) at the Norfolk and Norwich University Hospital.

##### Procedure 1: Establishment of study eligibility ~ participant visit 1

The first procedure will comprise a screening visit where written informed consent will be obtained and eligibility criteria will be established. Demographic status and medical history will be obtained by a researcher and documented in the case report form. Participants will undergo a clinical examination including examination of the respiratory (including anterior rhinoscopy) and cardiovascular system by a medically qualified investigator. Nasal symptom scores will be obtained and 10 ml peripheral blood taken for routine biochemistry and haematology. Participants will undergo a baseline nasal allergen challenge to determine the dose required to elicit a positive clinical reaction. Asthmatic participants will undergo spirometry. Asthma will be diagnosed as a clinical diagnosis by a medically qualified investigator based on the participants clinical history including details of participant-reported investigations and treatments. This procedure will take place between September and November.

##### Procedure 2: Pre-intervention baseline measurements ~ participant visits 2, 3 and 4

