## 5.2. Outline of Study Procedures

| Approximate dates in the year                                                                                                                                         | Sept – Dec | By end of Dec |     |      | By end Dec   | By end April |     |       | By Nov 201 <del>10</del>  |
|-----------------------------------------------------------------------------------------------------------------------------------------------------------------------|------------|---------------|-----|------|--------------|--------------|-----|-------|----------------------------------------|
|                                                                                                                                                                       | Screening  | Baseline      |     |      | Intervention | Follow up    |     |       | End                                    |
|                                                                                                                                                                       | Proc. 1    | Proc. 2       |     |      | Start        | Proc. 3      |     |       | Report                                 |
|                                                                                                                                                                       |            | Day1          |     | Day2 |              | Day 1        |     | Day 2 |                                        |
|                                                                                                                                                                       |            | 0hr           | 8hr | 24hr |              | 0hr          | 8hr | 24hr  |                                        |
| Written consent                                                                                                                                                       | x          |               |     |      |              |              |     |       |                                        |
| Inclusion/exclusion criteria                                                                                                                                          | x          |               |     |      |              |              |     |       |                                        |

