| Demographic status and medical history                                                                                                                                | x          |               |     |      |              |              |     |       |                                        |
| Clinical examination                                                                                                                                                  | x          | x             |     |      |              | x            |     |       |                                        |
| Skin prick test for common inhaled allergens                                                                                                                          | x          |               |     |      |              |              |     |       |                                        |
| Total nasal and allergic rhinitis symptom scores                                                                                                                      | x          | x             | x   | x    |              | x            | x   | x     |                                        |
| Peak nasal inspiratory flow                                                                                                                                           | x          | x             | x   | x    |              | x            | x   | x     |                                        |
| Initial intranasal allergen challenge                                                                                                                                 | x          |               |     |      |              |              |     |       |                                        |
| Spirometry (asthmatic participants only)                                                                                                                              | x          | x             | x   | x    |              | x            | x   | x     |                                        |
| Modified intranasal allergen challenge                                                                                                                                |            | x             |     |      |              | x            |     |       |                                        |

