## 5.10 Study Sequence

### 5.10.1 Study Procedure 1: *participant visit 1 ~ Screening Visit*

Once informed consent is obtained, clinical history and examination will be performed and eligibility criteria will be checked. Eligible participants will be recruited

to the trial. This procedure will take place between September and December 20~~1009~~. The following measurements will be performed:

- Skin Prick Allergy Test
- Routine biochemistry and haematology
- Total Nasal Symptom Scores
- Intranasal Allergen Challenge
- Spirometry (participants with asthma only)

Haematology will include haemoglobin, platelet count, white blood count and differential white blood count. Biochemistry will include renal function (Sodium, potassium, urea and creatinine) and liver function (albumin, bilirubin, alkaline phosphatase, alanine transaminase).

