#### 5.10.2 Study Procedure 2: *participant visits 2, 3 and 4 ~ Baseline tests*

Procedure 2 will take place at least 2 weeks after procedure 1, and no later than December for isolated grass pollen allergy or November for participants with grass and tree pollen allergy. This procedure entails participant visits on two consecutive days with baseline measurements being taken initially (visit 2) and nasal samples being obtained at 6-8 hours (visit 3) from a subgroup of participants and at 24 hours (visit 4) from all participants after nasal allergen challenge.

The subjects will undergo a clinical examination. Baseline measurements will be the following:

- Total Nasal Symptom Scores
- Peak Nasal Inspiratory Flow (PnIF)
- Modified Intranasal Allergen Challenge
- Nasal lavage, nasal scrapings and peripheral blood
- Spirometry and asthma symptom scores (participants with asthma only)

Nasal lavage, nasal scraping and 20ml (approximately 4 teaspoons) peripheral blood will be obtained before and 24 hours after nasal allergen challenge. Nasal lavage will also be taken 30 minutes after allergen challenge and, in a subgroup, 6-8 hours after allergen challenge

- Characterisation of cells derived from nasal scrapings
- Epithelial and peripheral blood cell culture and analysis of TSLP, cytokines, chemokines and soluble cytokine receptors and sCD23 following *in vitro* allergenic challenge
- Eotaxin, MIP-1 $\alpha$  and RANTES in nasal lavage
- Differential counts of cells derived in nasal lavage and nasal scrapings

Participants with isolated grass pollen allergy will attend for procedure 2 no later than December 20~~1009~~.

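### Pregnancy is excluded because of the risk from anaphylaxis, but it is checked only at screening and not before the two later allergen challenges

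*Protocol*

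**What the plan says.** Section 5.3.4 of the protocol lists as an exclusion "Pregnant women or those planning a pregnancy" and explains it: "It is important not to include pregnant women in the study due to the possibility of miscarriage following anaphylaxis".

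The check on this criterion belongs to the screening visit. Section 5.10.1 states: "Once informed consent is obtained, clinical history and examination will be performed and eligibility criteria will be checked". In the schedule table of Section 5.2, the rows "Inclusion/exclusion criteria" and "Demographic status and medical history" are marked in the screening column and nowhere else. The screening blood tests in Section 5.10.1 are haematology, renal function and liver function; no pregnancy test is listed.

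Allergen is given three times: as an escalating titration at screening (Section 6.5), then as a single individual dose at Procedures 2 and 3 (Section 6.6). On timing, Section 5.10.2 says "Procedure 2 will take place at least 2 weeks after procedure 1", and Section 5.10.6 puts Procedure 3 16 weeks after Procedure 2. Section 5.1 bounds the whole: "Participants will attend on 5 to 7 occasions over a 4 to 6 month period for three procedures".

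For Procedure 2, Section 5.10.2 says "The subjects will undergo a clinical examination", with no stated content on pregnancy. The schedule also marks an examination at Procedure 3.

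**The concern.** The reason given for the exclusion attaches to exposure to allergen, not to the date of enrolment. A check made once, before the first of three exposures, does not protect against the named harm at the second and third.

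Staff who follow the schedule exactly could give one or two further challenges to a woman who conceived after screening, with no prompt to ask about pregnancy and no instruction to withhold the allergen. Men and women over 16 are eligible (Section 5.3.3), so women who could become pregnant will be among the participants. What is at stake is participant safety.

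**Working it through.** **Comparison of the sections**

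| Condition | At screening | Before the later challenges |
|---|---|---|
| Eligibility criteria, medical history | Marked (5.2) | Not marked |
| Clinical examination | Marked (5.2) | Marked, no pregnancy element stated |
| Antihistamine abstention | Required (6.5) | Restated (5.10.6, 6.6) |
| Spirometry in asthmatics | Marked (5.2) | Marked |
| Pregnancy | Exclusion criterion (5.3.4) | Nothing stated |

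Avoidance of probiotics is likewise extended to the whole trial (Section 5.10.4). The protocol repeats or extends a condition where it wants it to last, and it does not do so for pregnancy.

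**Interval from the only check to each challenge**

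Inputs: at least 2 weeks from screening to Procedure 2 (5.10.2); 16 weeks from Procedure 2 to Procedure 3 (5.10.6); at most 6 months in total (5.1).

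- Shortest: 2 weeks to Procedure 2; 2 + 16 = 18 weeks to Procedure 3.
- Longest: 6 months = 182.6 days / 7 = 26.1 weeks to Procedure 3; 26.1 − 16 = 10.1 weeks to Procedure 2.

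The shortest total, 18 weeks, is a little over 4 months, which agrees with the lower end of the stated attendance period. The calendar limits taken alone would allow more. From 1 September to the end of November is about 13 weeks, and to the end of December about 17 weeks. Adding 16 weeks gives about 29 and 33 weeks to Procedure 3. The 10 and 26 weeks used here are therefore the cautious reading.

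**Dose**

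- Repeat dose, at most: 0.1 ml × 10,000 bau/ml = 1000 bau (6.5, 6.6).
- Screening titration, at most: 10 + 100 + 1000 = 1110 bau cumulative (6.5).

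The later challenge is thus no larger than what the same person has already received.

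**Expected conceptions, on assumed inputs**

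The protocol gives neither the number of women who could become pregnant nor a rate of unplanned pregnancy. I assume 15 to 30 women and 1% to 5% per year. Expected number = women × annual rate × weeks / 52.18.

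- Before Procedure 3: low 15 × 0.01 × 18 / 52.18 = 0.05; high 30 × 0.05 × 26.1 / 52.18 = 0.75.
- Of these, before Procedure 2: low 15 × 0.01 × 2 / 52.18 = 0.006; high 30 × 0.05 × 10.1 / 52.18 = 0.29.

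These are conceptions, not harms. Harm would also need a pregnancy that is unrecognised or not disclosed, anaphylaxis to the titrated dose, and then miscarriage.

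**The case against.** The best reply is that the protocol contains no false statement or contradiction here and that it deals with later pregnancy by selection. Excluding women who plan a pregnancy looks forward in time and can only be meant for the period after screening.

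Other safeguards exist. An examination is scheduled at each challenge visit, and a qualified medical practitioner is responsible for it (Section 11). Drinks are supplied every two weeks, so participants are not out of contact between Procedures 2 and 3. The repeat dose is individually titrated, expressly to avoid adverse events (Section 6.6). The participant information sheet mentioned in Section 5.5 is not shown and may tell women to report a pregnancy. The expected number of conceptions is below one even on the high assumptions, and a question will miss a woman who does not yet know that she is pregnant.

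All of this lowers the risk, and the low risk stands. None of it covers an unplanned conception after screening. The examination has no stated pregnancy content, the medical history is not repeated, and no enquiry is attached to the drink deliveries. Tolerance of the dose was shown before any such pregnancy, and the exclusion makes no exception for a titrated dose. The information sheet could help the participant, but it would not change the schedule that staff follow. A safety check before a challenge belongs in the protocol and is not something left to an analysis plan.

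**Conclusion.** The concern holds. The protocol ties the exclusion to a harm that can arise at every challenge but fixes the check at screening, leaving about 2 to 10 weeks before the second challenge and about 18 to 26 weeks before the third with no stated question or withhold rule. The lower bounds follow from the stated spacing of the procedures; the upper bounds rest on the 6-month attendance limit.

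The gap is confined to unplanned pregnancies that begin after screening. The figure of 0.05 to 0.75 conceptions depends wholly on the assumed inputs, and few if any of these would lead to harm. The change should be made because the harm is serious, the protocol itself names it, and the remedy is small. Confidence is moderate, since the information sheet is not visible.

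**What to change.** - **Section 5.2:** add a pregnancy-check row to the schedule, marked before the challenge at visits 2 and 5.
- **Sections 5.10.2 and 5.10.6:** state that each woman who could be pregnant is asked before the challenge, that the answer is recorded, and that the challenge is withheld if she is or may be pregnant. Where the answer is uncertain, a urine test the same day can settle it; this part is optional.
- **Handling:** a woman found pregnant at visit 2 is not randomised, since randomisation follows visit 4 (Section 5.1), and recruitment continues to 60 randomised (Section 5.4). A woman found pregnant at visit 5 stays in the randomised set, with the reason for the missing TNSS recorded.

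The cost is one table row and one question at two visits that already include an examination. If the optional test is adopted, the ceiling on the assumed numbers is 15 × 2 = 30 to 30 × 2 = 60 tests, and far fewer if used only for uncertain answers. An occasional Procedure 3 TNSS may be lost. The drop-out allowance can absorb this: 60 × 0.8 = 48 expected completers, against the 46 required.

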### 5.4 Randomisation

Stratified randomisation will be used. Such randomisation, by asthma and isolated grass allergy, would result in 4 different randomisation lists - one for individuals without asthma and without grass allergy, one for individuals with asthma but without grass allergy, one for individuals without asthma but with grass allergy and for individuals with both asthma and grass individuals - for each of which we shall use random permuted block randomisation (block sizes 4 and 6). Although this may result in a slight imbalance in the total number of individuals randomised to yakult or

control the maximum imbalance would be 3 individuals per strata. Study recruitment will stop when 60 individuals have been randomised.

## 5.5 Recruitment

Up to sixty participants with seasonal allergic rhinitis (SAR), will be recruited by advertisements within the Norwich Research Park campus, through the IFR) 'Human Studies' database, Respiratory Research Database, in the local press and via local GP surgeries. This is to have a completed sample size of 46 participants and allows for a 20% drop out rate.

All volunteers will be approached by the recruiting source (e.g GPs from GP surgeries and nurses at the Human Nutrition unit of IFR). They will have participant information sheets sent to them with their letter of invitation to participate in the study. Where recruits are obtained through advertisements within the Norwich Research Park campus or local press they will be invited to make contact with the Chief or Principal Investigators and on doing so will be sent relevant information by post. Due to time constraints in starting and completing the study before the following pollen season, it will not be possible to conduct face-to-face interactions with potential participants. However, the 'Participant Information Sheet' invites interaction by telephone with Drs. [name] or [name] for further study details, to answer any questions or address any concerns. This will be prior to visit 1. On expression of interest in participation, potential study participants will all be directed to [name], the Chief Investigator. Those volunteers wanting to participate in the study will be invited to visit the study nurses at the CTRU laboratory for face-to-face encounter when they will be able to ask any further questions about the study. If interest is retained following this they will sign consent forms and have their pre-study assessments performed.

## 5.6 Compliance

Compliance will be monitored through recovery of unused drinks at each delivery period. All study participants will also be provided with a calendar on which to record details of their intake of study drinks.

## 5.7 Regulatory Approval

Yakult has food product status in the UK and therefore this trial is not subject to regulation by the MHRA as a clinical trial.

The placebo is the same milk matrix as used in Yakult but without any *Lactobacillus* culture.

## 5.8 Ethics Review Committee

Approval from the Human Research Governance Committee at IFR (HRGC), a local Research Ethics Committee and the National Research Ethics Service (NRES) will be obtained before the study is commenced.

